#### Interventions: adherence

Online material was sent before the start of recruitment to the local investigators, research nurses, and treating physicians to explain the study hypothesis and the need for this study. Monthly newsletters have also been sent to promote the study and underline the importance for the adherence to the study protocol and active recruitment.

#### Interventions: concomitant care

No other limitations in concomitant care and interventions have been provided.

#### Explanation for the choice of comparators

In the absence of optimal Hb thresholds to initiate RBCT in this setting, an international survey was conducted to investigate at which Hb level clinicians would initiate RBCT in patients with acute brain injury [17]; among 868 responses, 54% reported an Hb threshold of 7–8 g/dL to initiate RBCT in this setting, although half of these respondents would use a different threshold (i.e., closer to 9 g/dL) in case of systemic and cerebral triggers. Moreover, one small randomized study including 44 TBI patients reported that Hb separation between these two strategies was feasible and resulted in less RBCT in the restrictive group [18].

## Objectives

Our primary research question is to determine whether a “liberal” strategy of maintaining Hb concentrations at 9 g/dL or higher would result in a different neurological outcome when compared to a “restrictive” approach to RBC transfusion maintaining Hb concentrations at 7 g/dL or higher in critically ill patients with anemia (Hb ≤ 9 g/dL) and acute brain injury. We expect fewer complications in the restrictive group but an improvement in brain oxygenation in the liberal group, with a potential impact on neurological outcomes.

## Trial design

We will perform a prospective, multicenter phase 3, two-arm, randomized, investigator-initiated, superiority, pragmatic, and open-label study in anemic (i.e., Hb ≤ 9 g/dL) patients with an acute brain injury. Allocation is in a 1:1 ratio.

## Methods: participants, interventions, and outcomes

### Study setting

This study will be conducted in 72 intensive care units (ICUs) worldwide. The complete list of recruiting sites is shown in Supplemental Table 1. The selection of participating ICUs was initiated within the Neuro-Intensive Care (NIC) Section of the European Society of Intensive Care Medicine (ESICM), with the identification of national investigators who then selected potential academic and non-academic ICUs with neurosurgical facilities and an adequate number of patients (> 50) with acute brain injury admitted per year. The study was initially expected to last 4 years, assuming the inclusion of 75–95 patients/month in 50–70 different centers. The final duration of the study will be almost 7 years, because of the slow recruitment rate, which is in part due to the recent pandemic crisis.

**Table 1 Tab1:** Inclusion and exclusion criteria of the TRAIN study

Inclusion criteria	Exclusion criteria
TBI, SAH, or ICH	Other neurological diseases, such as ischemic stroke or post-anoxic coma; status epilepticus without underlying brain injury; CNS infections (community-acquired; hospital-acquired; ventriculitis; post-operative)
Age ≥ 18 and ≤ 80 years	
GCS ≤ 13 on randomization	Known previous neurological disease, causing significant cognitive and/or motor handicap
Expected ICU stay > 72 h	ICH due to AVM or brain tumor
Hb ≤ 9 g/dL within 10 days from brain injury	Inability (religious reasons) or reduced ability (lack of compatible blood) to receive blood products
	Active and uncontrolled bleeding at the time of enrollment
	GCS of 3 with both pupils fixed and dilated; brain death or imminent death (within 24 h)
	Pregnancy
	Medical need to correct anemia (e.g., active coronary disease or severe cardiac disease) with target Hb levels > 9 g/dL
	DNE orders
	Previous allo-immunization due to transfusion, limiting RBC availability

*GCS*, Glasgow Coma Score; *ICU*, intensive care unit; *Hb*, hemoglobin; *DNE*, do-not-escalate (i.e., vasopressors, mechanical ventilation, renal replacement therapy); *CNS*, central nervous system; *ICH*, intracranial hemorrhage; *AVM*, arterio-venous malformation; *TBI*, traumatic brain injury; *SAH*, subarachnoid hemorrhage

### Eligibility criteria

All patients admitted to the ICU with TBI, SAH, or intracerebral hemorrhage (ICH, either primary or anticoagulant-associated) are screened for study eligibility within the first 10 days after the initial injury. Patients are eligible regardless of their need for surgical intervention or RBCT for acute bleeding. Anemia is defined as Hb ≤ 9 g/dL and should occur within this time period. If a patient is considered as not eligible, the reason is recorded as for eligible patients who decide not to participate. No other specific information is recorded for such patients. Inclusion and exclusion criteria are shown in Table 1 and are checked by the attending physician and confirmed by the local investigator.

### Who will take informed consent?

Research nurses or local investigators will introduce the study to the legal representatives (i.e., patient’s next of kin, legal guardian) explaining the main issues of the trial. All aspects of the trial will be discussed with the legal representatives and an informed discussion with be undertaken. Research nurses or local investigators will obtain written consent from legal representatives willing to let the patient participate to the trial. A copy of the informed consent will be given to the legal representative. The information and consent forms are part of a unique document. Small changes might happen to this procedure, according to legal requirements in different countries.

### Provisions for post-trial care

There is no anticipated harm and compensation for trial participation, since the transfusion thresholds that will be compared are already variably used in routine care.

### Study outcomes

The primary outcome measure is the proportion of patients with unfavorable neurological outcome at 180 days after randomization, assessed using the eGOS and dichotomized as “unfavorable” (eGOS 1–5) or “favorable” (eGOS 6–8). This scale has been largely used to assess neurological outcome in different interventional randomized trials dealing with acute brain-injured patients; mortality is part of the scale (eGOS 1).

Secondary outcome measures are (1) 28-day survival; (2) eGOS distribution between the two groups (i.e., ordinal outcome analysis); (3) ICU and hospital lengths of stay; (4) presence and severity of extra-cerebral organ dysfunction/failure, assessed using the daily Sequential Organ Failure Assessment (SOFA) score; (5) infection rate, except those involving only the central nervous system (CNS); (6) composite outcome (death and/or organ dysfunction/failure); (7) fluid balance; and (8) for centers monitoring brain tissue oxygenation (PbtO_2_), time spent with P_bt_O_2_ < 20 mmHg (brain hypoxic burden) will also be collected and analyzed, but reported into a separate secondary analysis.

### Participant timeline

The participant timeline is reported in Fig. 1.

**Fig. 1 Fig1:**
[figure not shown]
Study flow diagram. Hb, hemoglobin; TBI, traumatic brain injury; SAH, subarachnoid hemorrhage; ICH, intracerebral hemorrhage; GCS, Glasgow Coma Scale; ICU, intensive care unit; eGOS, extended Glasgow Outcome Scale

### Sample size

The primary outcome measure of this study is the occurrence of unfavorable neurological outcome at 180 days, evaluated by a eGOS of 1–5. To calculate the sample size, we estimated a mortality rate of 15% and a percentage of poor neurological outcome of 35% (i.e., eGOS 1–5 of 50%). There are no specific epidemiological data to support this assumption, as the population is mixed (i.e., TBI, SAH, and ICH) and the proportion of patients being eligible for the study remains unknown. Thus, the initial sample size calculation identified a total of 2095 patients needed to be recruited for each arm to achieve a power of 90% at a two-sided alpha level of 0.05 or less to detect a reduction of poor outcome rate at 180 days from 50 to 45% (absolute reduction of 5%, i.e., 10% relative reduction) in one of the two arms. Sample size calculation was adjusted twice. The first change (approved in August 2019) consisted in considering a reduction in unfavorable neurological outcome rate at 180 days from 50 to 40% (absolute reduction of 10%, i.e., 20% relative reduction, *n* = 1000) in one of the two arms, considering the relatively low number of patients being eligible for the study. The second change (approved in June 2022) consisted in considering a reduction in unfavorable neurological outcome rate at 180 days from 50 to 39% (absolute reduction of 11%, i.e., 22% relative reduction, *n* = 756–378 patients per group) in one of the two arms, with a power of 85% and at a two-sided alpha level of 0.05. Considering a potential 5% lost to follow-up, a total of 794 patients (397 per group) are needed to complete the study. This last modification was decided because of the coronavirus disease 2019 (COVID-19) pandemic, which significantly disrupted recruitment and blood availability and led to uncertainty over future recruitment.

### Recruitment

All adult ICU patients with a TBI, SAH, or ICH and having an Hb value of 9 g/dL or less within the first 10 days since admission can be considered for enrolment; they will be included and randomized by local investigators. The estimated recruitment is 0.1–0.2 patient per center per month, within an expected recruitment period of 6 years; however, this estimation is largely influenced by the COVID-19 pandemic, the active participation of each center, and the different timing of ethics approval in all countries.

## Methods: assignment of interventions

### Assignment of interventions: allocation

## Sequence generation

All eligible acute brain-injured patients during the study period in one of the participating centers can be considered for enrolment in the study. Randomization is performed using a computer-generated random sequence (variable blocks of 4, 6, and 8), stratified by center, by disease (TBI, SAH, or ICH), and by the Glasgow Coma Scale (GCS) at the moment of randomization (3–5; 6–9; 10–13).

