## Methods: data collection and management

### Plans for assessment and collection of outcomes

Data collection on admission will include the following: demographic characteristics, comorbidities, source of admission, primary and secondary admission diagnoses, Acute Physiologic Assessment and Chronic Health Evaluation (APACHE) II score (the worst values of the first 24 h), Sequential Organ Failure Assessment (SOFA) score on admission, GCS immediately after injury, GCS on hospital admission after initial resuscitation, initial Hb concentration, and sodium and glucose levels.

For patients with TBI, the following data are also collected: Marshall score on cerebral CT scan (the worst of the first 24 h), presence of traumatic SAH and/or epidural mass on CT scan, pupillary reactivity, mechanisms of injury, hypoxemia (defined as a SpO_2_ < 90% for more than 5 min with or without endotracheal intubation and under oxygen therapy) and/or hypotension (defined as a systolic blood pressure < 90 mmHg for more than 5 min despite fluid resuscitation) before or on hospital arrival, intracranial pressure (ICP) monitoring within the first 48 h, and previous therapy with antiplatelet drugs or anticoagulants.

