Data on each transfused RBC unit during the ICU stay and premature study termination (documenting the reason and time of termination) are recorded. In case of death, reasons for withdrawal of care are collected. ICU and hospital lengths of stay, the duration of mechanical ventilation over the first 28 days (either by endotracheal tube or tracheostomy), the need for tracheostomy on ICU discharge, and location of discharge after a hospital stay (home vs. rehabilitation vs. nursing home) are recorded. Follow-up at 180 days for primary outcome measure assessment is performed.

Data will be collected and stored as described at point 19, into the eCRF. After 6 months, patients who are still alive will be contacted by phone or by face-to-face meeting, according to local practice, for a structured interview to obtain the eGOS scale. The eGOS is widely used to assess neurological outcome in this setting [19].

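### The adjusted primary analysis and the severity subgroup rest on the GCS at randomization alone; the post-resuscitation GCS, already collected, should be added to both

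*Protocol article*

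**What the plan says.** Four parts of the protocol article depend on one GCS value.

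- Entry (Table 1, under Study setting): "GCS ≤ 13 on randomization".
- Strata (Sequence generation): besides center and disease, allocation is stratified "by the Glasgow Coma Scale (GCS) at the moment of randomization (3–5; 6–9; 10–13" points).
- Adjusted primary analysis (Statistical methods: outcomes): the covariates are the stratification criteria, so severity enters as the GCS at randomization.
- Severity subgroup (Statistical methods: additional analyses): again the GCS at randomization, in bands 3–5, 6–8 and 9–11.

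On timing, patients "are screened for study eligibility within the first 10 days after the initial injury", and Table 1 requires "Hb ≤ 9 g/dL within 10 days from brain injury".

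The section Plans for assessment and collection of outcomes also lists "GCS immediately after injury, GCS on hospital admission after initial resuscitation" among the admission data. The article names neither score for entry, strata, adjustment or subgroup.

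**The concern.** Randomization is triggered by hemoglobin, not by neurological state, so the GCS is scored whenever anemia happens to appear. In an ICU patient on that day, a low score may mean severe brain injury, recent deterioration, sedatives, a tracheal tube that prevents verbal scoring, or a mixture of these.

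This matters in two places. A covariate that mixes injury with drug effect explains less of the 180-day outcome than it could, so the adjusted estimate gains less from it. And a treatment effect that varies across bands of this score cannot be read simply as varying with the severity of the injury. A score taken at hospital admission after resuscitation is already in the database and carries partly different information.

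**Working it through.** The plan gives no figure on this point, so the check consists of comparing the sections.

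**1. Which score is used where.**

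| Use | Section | GCS used |
|---|---|---|
| Entry, ≤ 13 | Table 1 | at randomization |
| Strata 3–5, 6–9, 10–13 | Sequence generation | at randomization |
| Covariate in adjusted primary analysis | Statistical methods: outcomes | at randomization, as a stratification criterion |
| Subgroup 3–5, 6–8, 9–11 | Statistical methods: additional analyses | at randomization |
| No use named | Plans for assessment and collection of outcomes | after injury; after resuscitation |

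**2. Can the score at randomization reflect more than brain injury?** Yes. Table 1 requires an expected ICU stay above 72 h, and Eligibility criteria admits patients whether or not they need surgery. The article records "the duration of mechanical ventilation over the first 28 days" and lists barbiturates among second-tier therapies for raised intracranial pressure. Its definition of delayed ischemic deficit requires excessive sedation to be ruled out first, so the authors recognize that sedation distorts the neurological examination. The only exclusion that depends on a GCS value is "GCS of 3 with both pupils fixed and dilated", so a drug-related score of 3 with reactive pupils would not be excluded. None of this gives a frequency. It shows that the situation can occur, not how often.

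**3. Does it bias the comparison?** No. The score is taken before allocation and under the same rule in both arms. The main primary test is an unadjusted chi-square, which does not use the score.

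**4. Can a size be given?** Suppose a share *s* of the 3–5 stratum is there because of sedation. The stratum risk of an unfavorable outcome is then

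risk = r_true × (1 − *s*) + r_sed × *s*.

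With assumed values r_true = 0.75 and r_sed = 0.45:

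- *s* = 0.3: 0.75 × 0.7 + 0.45 × 0.3 = 0.525 + 0.135 = 0.66
- *s* = 0.5: 0.75 × 0.5 + 0.45 × 0.5 = 0.375 + 0.225 = 0.60

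None of these inputs comes from the article. It gives no risk for the other two strata either, so even with these values a loss of separation between strata cannot be derived. The formula shows the mechanism and gives no estimate.

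**5. Is the post-resuscitation GCS a legitimate covariate?** Yes. It is recorded at hospital admission, before randomization, so allocation cannot affect it. The entry limit of 13 applies only to the score at randomization, so this earlier score may also be 14 or 15, and any grouping of it must cover that range.

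**The case against.** The other side has a strong case, and most of it stands.

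- The text is a condensed article. How to score a sedated or intubated patient is the kind of detail left to the full protocol or the eCRF guide, so the absence of such a rule is not a fault. This stands.
- The current GCS is a defensible choice. The intervention may start days after injury, and a current score captures deterioration that an admission score misses. This stands, and it is why the current score should be kept.
- Trial status reports 791 patients recruited against a target of 794. Redefining entry or strata would change almost nothing. This stands.
- Covariates belong in an analysis plan that is not shown. This stands only in part: the article itself says what the primary outcome is adjusted for and which score defines the subgroup, and those stated choices are the ones at issue.

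A reader might go further and infer that mildly injured, sedated patients enter the trial against its intent, pull the event rate away from the assumed 50%, and leave the 3–5 stratum of little prognostic use. The article does not support this. It gives no share of sedated patients, and the other entry criteria still apply. Sample size says the 50% has no specific epidemiological data behind it, so there is no firm rate from which to measure a departure. With the assumed values in the working, sedated patients have a 45% risk, close to the overall 50%, and the stratum stays at 60% or more.

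**Conclusion.** The point holds in a limited form. The adjusted primary analysis and the severity subgroup rely on a single neurological severity score whose meaning on the day of randomization is uncertain, while an earlier score already in the database goes unused. The randomized comparison and the unadjusted primary test are unaffected. The cost is a possible loss of precision in the adjusted estimate and a severity subgroup that is harder to interpret.

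The size cannot be stated from the document. The conclusion rests on two assumptions: that some patients were sedated or intubated when scored, which the recorded therapies make plausible, and that the post-resuscitation GCS predicts outcome beyond the score at randomization. It does not rest on the absence of a scoring rule, and it is no reason to question eligibility or the strata.

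**What to change.** Leave eligibility and strata as randomized. Then make two additions before the treatment groups are unblinded:

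1. In Statistical methods: outcomes, name the post-resuscitation GCS as a pre-specified covariate alongside the stratification factors, fixing in advance how it enters the model and how a missing value is handled.
2. In Statistical methods: additional analyses, repeat the severity subgroup on the post-resuscitation GCS as a supporting analysis, with cut points fixed beforehand that cover the whole range, including 14 and 15.

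The score is already collected, and data collection was planned to run to June 2023. The cost is a little more analysis work and one more subgroup table. The earlier score may miss deterioration before randomization, and it may itself have been taken after intubation in some patients. For these reasons it supplements the score at randomization and does not replace it.

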## Concealment mechanism

Randomization will be performed using the online eCRF; if the subject meets all inclusion and exclusion criteria, the investigator will include some baseline characteristics and the randomization treatment arm will be provided by the web-based system (ClinFile, https://clinfile.com).

## Implementation

Investigators of all participating centers can sign into the web-based randomization system and randomize their patients. Patients will be automatically allocated to one of the treatment arms by the system.

## Assignment of interventions: who will be blinded?

Neither ICU nor hospital personnel is blinded to the treatment assignment, because patients are easily distinguishable by routine daily assessment of Hb concentrations. However, the final neurological evaluation of the patient is performed by assessors who are blinded to the group assignment.

### Procedure for unblinding if needed

As the study is open-label, no indications for breaking the randomization code are provided in the protocol. Randomization is communicated from the local principal investigator of each participating hospital to the study team. Based on the Hb daily levels achieved, concealed allocation can be controlled.

## Methods: data collection and management

### Plans for assessment and collection of outcomes

Data collection on admission will include the following: demographic characteristics, comorbidities, source of admission, primary and secondary admission diagnoses, Acute Physiologic Assessment and Chronic Health Evaluation (APACHE) II score (the worst values of the first 24 h), Sequential Organ Failure Assessment (SOFA) score on admission, GCS immediately after injury, GCS on hospital admission after initial resuscitation, initial Hb concentration, and sodium and glucose levels.

For patients with TBI, the following data are also collected: Marshall score on cerebral CT scan (the worst of the first 24 h), presence of traumatic SAH and/or epidural mass on CT scan, pupillary reactivity, mechanisms of injury, hypoxemia (defined as a SpO_2_ < 90% for more than 5 min with or without endotracheal intubation and under oxygen therapy) and/or hypotension (defined as a systolic blood pressure < 90 mmHg for more than 5 min despite fluid resuscitation) before or on hospital arrival, intracranial pressure (ICP) monitoring within the first 48 h, and previous therapy with antiplatelet drugs or anticoagulants.

For patients with SAH, the following data are also collected: World Federation of Neurological Society (WFNS) score; Fisher CT-scan scale; ICP monitoring within the first 48 h; pupillary reactivity on arrival; hydrocephalus; diagnosis of vasospasm (either using trans-cranial Doppler [TCD], contrast CT scan, and/or angiography); development of delayed neurological ischemic deficit (DNID); therapies for DNID; and occurrence of DCI. TCD-vasospasm is defined as a mean flow velocity in any vessel > 200 cm/s or > 120 cm/s and a Lindegaard ratio > 3 [22]. Angiographic or contrast CT-scan vasospasm is defined by a neuroradiologist as moderate-to-severe arterial narrowing (> 50%) on specific imaging not attributable to atherosclerosis, catheter-induced spasm, or vessel hypoplasia. Definition of DNID is based on the development of new focal neurological signs, deterioration in the level of consciousness, or both, when the cause is felt to be ischemia attributable to vasospasm after other possible causes of worsening (e.g., hydrocephalus, seizures, metabolic derangement, infection, or excessive sedation) have been excluded [23]; as such, DCI is defined as the appearance of DNID and/or a new infarction on cerebral CT scan or magnetic resonance imaging (MRI), when the cause was attributed to vasospasm [23].

For patients with ICH, the following data are collected: ICH volume > 30 mL on the initial CT scan (measured/estimated by local neuroradiologist); the presence of intra-ventricular hemorrhage; location (deep, cortical, infratentorial); ICP monitoring within the first 48 h; and pupillary reactivity on arrival.

Daily data collection (only during the ICU stay) includes daily GCS score; Hb concentration (minimum and maximum); sodium and glucose levels at 8 am (or the first value of the day); ICP levels at 8 am (or the first value of the day); maximum ICP levels during the day; SOFA score; the presence of infection (location, pathogen, treatment); the presence of sepsis; the occurrence of serious adverse events (*see paragraph on adverse events*); the need for second-tier therapies for increased ICP (hypothermia; barbiturates; decompressive craniectomy) or seizures (convulsive or non-convulsive); and daily fluid intake and urine output (to calculate daily fluid balance).

Data on each transfused RBC unit during the ICU stay and premature study termination (documenting the reason and time of termination) are recorded. In case of death, reasons for withdrawal of care are collected. ICU and hospital lengths of stay, the duration of mechanical ventilation over the first 28 days (either by endotracheal tube or tracheostomy), the need for tracheostomy on ICU discharge, and location of discharge after a hospital stay (home vs. rehabilitation vs. nursing home) are recorded. Follow-up at 180 days for primary outcome measure assessment is performed.

Data will be collected and stored as described at point 19, into the eCRF. After 6 months, patients who are still alive will be contacted by phone or by face-to-face meeting, according to local practice, for a structured interview to obtain the eGOS scale. The eGOS is widely used to assess neurological outcome in this setting [19].

